### Interim analyses {21b}

This is not applicable as this is not a pharmaceutical trial.

### Methods for additional analyses (e.g., subgroup analyses) {20b}

We will examine potential mediation of the intervention effect by [1] MVPA and [2] fear avoidance of concussive symptoms We plan to conduct two sets of mediation analyses. The first set of mediation analyses will focus on the changes between baseline and 3 months. The main motivation for this choice is that this analysis amounts to a conventional single mediator model which is easy to implement and has a simple interpretation, directly addressing questions such as, “How much of the effect of MSTEP on improved concussive symptoms is mediated through increased MVPA or decreased fear avoidance?” We will use residualized change scores instead of the difference scores in part because they adjust for baseline differences and avoid some of the problems with the reliability of difference scores. The residualized change score is the difference between the observed score at 3 months and predicted score at 3 months, where baseline score is used to predict 3-month score. With residualized change scores calculated for mediators (MVPA and FOPQ) and outcomes (HBI, PedsQL), we can proceed to the standard single mediator model as depicted in the following figure. The mediation model can be represented using the three ordinary-least-squares (OLS) regression equation: *Y*_*i*_ = *i*_1_ + *cX*_*i*_ + *ϵ*_1*i*_; *M*_*i*_ = *i*_2_ + *aX*_*i*_ + *ϵ*_2*i*_; *Y*_*i*_ = *i*_3_ + *c*^′^*X*_*i*_ + *bM*_*i*_ + *ϵ*_3*i*_, where *c* is the total effect of *X* on *Y*, *c’* is the direct effect of *X* on *Y* controlling for *M*, *a* is the effect of *X* on *M*, *b* is the effect of *M* on *Y* controlling for *X*, and *ab* is the mediated effect. Significance of mediated (indirect) effect can be tested via Sobel test or bootstrap methods [100].

The second set of mediation analyses will be longitudinal mediation using a latent growth curve modeling (LGCM) framework, allowing us to utilize the repeated assessments and therefore provide more insight into the mediation process, while allowing more accurate functional forms. Step 1: The growth trajectories of mediator and outcome are modeled separately to determine the trajectory shapes and estimate the overall changes in the mediator and the outcome. In the following, we assume exponential decay trajectories for both mediator process and outcome process, although different forms can be assumed. The measurement models can be specified as: ***Mediator Process :*** *M*_*ij*_ = *β*_2*i*_ + (*β*_0*i*_ − *β*_2*i*_) exp(−*β*_1*i*_*t*_*j*_) + *e*_*ij*_
$$ \boldsymbol{Outcome}\ \boldsymbol{process}:{Y}_{ij}={\gamma}_{2i}+\left({\gamma}_{0i}-{\gamma}_{2i}\right)\exp \left(-{\gamma}_{1i}{t}_j\right)+{e}_{ij} $$

Step 2: Mediational process is then modeled by combining the two growth curve models and relating the growth factors (random effects *β*’s and *γ*’s) and the independent variable *X* (group assignment) in the structural model expressed as follows:
$$ {\beta}_{0i}={b}_0+{a}_0{X}_i+{\xi}_{0i} $$$$ {\beta}_{1i}={b}_1+{\eta}_2{\gamma}_{0i}+{a}_1{X}_i+{\xi}_{1i} $$$$ {\beta}_{2i}={b}_2+{\eta}_3{\gamma}_{0i}+{a}_2{X}_i+{\xi}_{2i} $$$$ {\gamma}_{0i}={g}_0+{c}_0{X}_i+{\epsilon}_{0i} $$$$ {\gamma}_{1i}={g}_1+{\eta}_4{\beta}_{0i}+{\eta}_5{\beta}_{1i}+{\eta}_6{\beta}_{2i}+{c}_1{X}_i+{\epsilon}_{1i} $$$$ {\gamma}_{2i}={g}_2+{\eta}_7{\beta}_{0i}+{\eta}_8{\beta}_{1i}+{\eta}_9{\beta}_{2i}+{c}_2{X}_i+{\epsilon}_{2i} $$

These equations posit that [1] the initial state of outcome process (*γ*_0_) affects rate of change (*β*_1_) and asymptote (*β*_2_) of the mediator process [2]; initial state, rate of change, and asymptote of moderator process affect both rate of change and asymptote of the outcome process. The single mediator model and longitudinal mediation model using LGCM will be implemented estimated using M-Plus and R statistical software.

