### Trial design {8}

Youth with PPCS will be randomized to 6 weeks of either MSTEP (a virtually delivered subthreshold exercise program) or an active control (stretching). This is a superiority trial, testing whether MSTEP is superior to the active control. Randomization will be allocated 1:1 to MSTEP and control, stratified by severity of concussive symptoms and sex at birth. Data will be collected at baseline, weekly during the intervention and at 6 weeks, 3 months, and 6 months.

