### Sample size {14}

We plan to recruit 200 subjects. Given the RCT design and repeated assessments, we calculate power for our primary outcomes (HBI) and (PedsQL) using two-way repeated analysis of variance (ANOVA) with two factors: study group is the between-subject factor, and time point (baseline, 6 weeks, 3 months, and 6 months) is the within-subject factor. To address our main hypothesis of differences in trajectories, we will test the between-within interaction effect, i.e., the interaction between study group and time. If we were to see similar differences in means between the two study groups on HBI and PedsQL as we did in our pilot STEP RCT [16], our planned sample size of 200 would provide > 99% power to detect a significant group-by-time interaction (i.e., differences in trends over time between the groups) in both HBI and PedsQL. This estimate is based on 4 time points, similar but slightly larger variances as we observed in pilot data, and an ICC = 0.5 for moderate within-subject correlations. We also wanted to ensure we would have sufficient power to assess mediation. For this power calculation, we used the regression model approach for single mediator. Vittinghoff [98] showed that for the linear regression, $$ {y}_i={b}_0+{b}_1{x}_i+{b}_2{m}_i+{\epsilon}_i,{\epsilon}_i\sim N\left(0,{\sigma}_e^2\right), $$ testing the mediation effect is equivalent to testing the null hypothesis *b*_2_ = 0 versus the alternative hypothesis *b*_2_ ≠ 0. The sample size depends on power, type I error rate, regression coefficient *b*_2_, standard deviation of the mediator *σ*_*m*_, standard deviation of the error term in the above regression *σ*_*e*_, and the correlation between the predictor *x* and the mediator *m, ρ*_*xm*_. Using residualized change scores from our pilot data for the outcome (HBI) and mediators (MVPA and FOPQ) [16], we found that if we were to observe similar mediation effects from MVPA levels and FOPQ as in our pilot data, our proposed total sample size of 200 would provide 78% power to assess mediation by MVPA and 95% power to assess mediation by FOPQ.

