## Statistical methods

### Statistical methods for primary and secondary outcomes {20a}

The primary outcome analyses will be assessed using intention-to-treat with the predictor of interest being experimental group regardless of adherence with assigned treatment. We will examine the impact of adherence on treatment effects in secondary analyses. Pre-identified potential confounders such as demographics (age, sex, and body mass index [BMI]), baseline biopsychosocial factors (standardized measures of depression and anxiety [PHQ-9 and GAD-7]), baseline clinical factors (history of prior concussion, severity of symptoms, duration of symptoms at entry into the study, outcome measures at baseline), and parental protective behavior (Adult Responses to Children’s Symptoms, ARCS) will be summarized using descriptive statistics. In addition to stratification factors (age, sex, and severity of symptoms), we make the a priori decision to control for biopsychosocial factors, particularly parental protective behavior, as well as any other unbalanced confounders from the list above as independent predictors in all subsequent regression analyses. We will model and compare trajectories of outcome measures using mixed effects models. We choose mixed effects modeling for its ability to account for variation at different levels, flexibility regarding time trend and unequally spaced time points, and ease with management of missing data.

The first part of the primary analysis will examine differences in HBI and PedsQL (primary outcomes) between study arms post-intervention (6 weeks) and follow-up (6 months) respectively. The main analytic tool will be based on covariate-adjusted regression models. The two primary outcomes can be considered as continuous outcomes thus linear regression models will be applied, in which group assignment will be the predictor of interest and other pre-identified confounders will be adjusted as covariates.

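### The 3-month mediation model residualises each score on its own baseline only and does not secure adjustment for the other baseline or for time since injury, so path b can be biased

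*Protocol article*

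**What the plan says.** Section 20b plans two sets of mediation analyses. The first is a single-mediator model for change from baseline to 3 months. Its scores are justified as follows: "We will use residualized change scores instead of the difference scores in part because they adjust for baseline differences". Each score is the observed 3-month value minus a predicted one, "where baseline score is used to predict 3-month score". Three ordinary-least-squares equations follow: Y on X, M on X, and Y on X and M. No covariate term is printed. The indirect effect ab is tested by the Sobel test or a bootstrap.

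The second set, in the same section, is a latent growth model. It lets the initial outcome affect the mediator's rate of change and asymptote, and lets the initial mediator affect those of the outcome.

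Section 20a sets a general covariate rule. Stratification factors (listed there as age, sex and symptom severity) and biopsychosocial factors, especially parental protectiveness, are controlled a priori. Other listed confounders are added if unbalanced. All of these enter "as independent predictors in all subsequent regression analyses". The list includes symptom duration at entry and the outcome measures at baseline. It does not include baseline MVPA or FOPQ.

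The sample size section gives the mediation analysis its own power: 200 participants "would provide 78% power to assess mediation by MVPA and 95% power to assess mediation by FOPQ".

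**The concern.** Randomisation makes the effects of group on the mediator (a) and on the outcome (c) unconfounded. It does nothing for b, the association between mediator and outcome within arms. Three features leave b exposed.

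- **Different baselines are removed from the two scores.** Regressing one residual on another reproduces the adjusted coefficient only if the same variables are removed from both. Here the mediator score still carries baseline outcome, and the outcome score still carries the baseline mediator.
- **The covariate rule in 20a does not close this gap.** Baseline MVPA and FOPQ are not on its list, and continuous baseline outcome is assured only if unbalanced.
- **Symptom duration also depends on imbalance between arms.** Balance between arms says nothing about whether a variable confounds mediator with outcome. Entry is allowed from 1 week to 12 months after injury, and section 20a itself describes faster improvement in the first 3 months, then levelling off. Natural recovery could therefore drive HBI down while MVPA rises or fear falls. The link to MVPA and fear is plausible but not documented.

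Mediation is a stated objective and hypothesis, and the Discussion says the trial is powered for mechanisms so as to guide later treatment design. A biased b could hide a real mediator, or credit one with what is only natural recovery.

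**Working it through.** **Inputs from the protocol.** Sample size: "We plan to recruit 200 subjects". Allocation: "Randomization will be allocated 1:1 to MSTEP and control". Stated mediation power: 78% (MVPA) and 95% (FOPQ). Basis of that power: "Using residualized change scores from our pilot data for the outcome (HBI) and mediators (MVPA and FOPQ"). Type I error is named but has no value ("The sample size depends on power, type I error rate, regression coefficient"), so two-sided 0.05 is assumed.

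**1. The plan's own figure.** Power = Φ(√N · k − 1.960), with k = b₂ σ_m √(1 − ρ_xm²) / σ_e. The article does not print the four pilot inputs, so the power can only be solved backwards:
- 78%: k = (1.960 + 0.772)/√200 = 2.732/14.142 = 0.193
- 95%: k = (1.960 + 1.645)/14.142 = 0.255

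These are the standardised effect sizes the trial is planned to detect. They are the yardstick for any bias.

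**2. Effect of own-baseline residualisation.** All values here are assumed. Baselines M0 and Y0 are standardised with correlation ρ. Own-baseline stability is λ = 0.5. Baseline outcome affects the 3-month mediator by κ, and baseline mediator affects the 3-month outcome by φ. Mediator error variance is s² = 0.5625. Then:
- Mediator residual = κ(Y0 − ρM0) + e
- Outcome residual = (bλ + φ)(M0 − ρY0) + b·e + independent error
- Cov(Y0 − ρM0, M0 − ρY0) = −ρ(1 − ρ²)

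So b_res = [b s² − (bλ + φ) κ ρ (1 − ρ²)] / [s² + κ²(1 − ρ²)].

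With b = 0.30, ρ = 0.5 and κ = φ = 0.2:
- Numerator: 0.16875 − 0.35 × 0.2 × 0.5 × 0.75 = 0.1425
- Denominator: 0.5625 + 0.04 × 0.75 = 0.5925
- b_res = 0.24

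| κ | φ | b_res (true b 0.30) |
|---|---|---|
| 0 | 0 | 0.30 |
| 0 | 0.2 | 0.30 |
| 0.1 | 0.1 | 0.28 |
| 0.2 | 0.2 | 0.24 |

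Over ρ 0.3–0.6, κ 0.1–0.3 and φ 0–0.2, b_res is 68% to 96% of the truth. In simulation at n = 200 with both cross-effects 0.2, the power to detect b was 90%, against 99% with both baselines in the model. With true b = 0 and the same cross-effects, rejection stayed at about 6%.

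**3. Effect of an omitted common cause.** Suppose time since injury correlates r with each baseline-adjusted 3-month score, acting in the direction of recovery on both, and true b = 0. The spurious standardised b is r × r. Approximate rejection is Φ(√200 · r²/√(1 − r⁴) − 1.960), plus a small opposite tail.

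| r | spurious b | rejection, formula | rejection, simulation |
|---|---|---|---|
| 0.2 | 0.04 | 9% | 9% |
| 0.3 | 0.09 | 25% | 25% |
| 0.4 | 0.16 | 63% | 61% |

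At r = 0.4 the spurious effect (0.16) approaches the 0.193 implied by 78% power. In simulation, adding the common cause to the model brought rejection back to about 5%. Adding both baselines without it did not.

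**The case against.** - **A reader might infer that no covariates enter the mediation models.** The documents do not support that. The 20a rule reaches every later regression, and these are later regressions. The text says only that the model can be represented by the three equations. The PedsQL model, for a primary outcome, is also printed without covariates. Age, sex, severity, PHQ-9, GAD-7 and ARCS therefore appear to be committed already. What is left is the baseline mediator, continuous baseline outcome and time since injury.
- **A reader might infer that b is biased.** The documents support only that it can be. They give no cross-effect, baseline correlation or correlation with time since injury. Residualisation alone gives no bias to modest attenuation, and almost no false-positive inflation at the values shown.
- **The larger error rates are not specific to residualised scores.** They come from mediator-outcome confounding, which any mediation analysis faces, and they assume that no committed covariate absorbs it. This is fair. It does not excuse making symptom duration depend on imbalance between arms.
- **The growth model already has the cross-baseline paths.** That is true, and the 3-month model is offered openly as the simple one. But its equations do not include time since injury. The protocol's own belief in those paths is also the best reason not to omit them from the simple model.
- **This is an additional analysis in a condensed article.** An article may leave details to the analysis plan. Here, though, the article states a specific residualisation method and a specific rule for admitting covariates.

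**Conclusion.** The concern holds in limited form. As specified, the 3-month analysis does not secure adjustment for the other variable's baseline or for time since injury, and randomisation does not protect b. Attenuation from 0.30 to about 0.24 rests on assumed cross-effects of 0.2 in both directions and a baseline correlation of 0.5. False-positive rates of about 9% to 61% rest on assumed correlations of 0.2 to 0.4 between time since injury and both scores, with nothing else in the model absorbing them. Neither set of values comes from the protocol, so the actual size and direction are unknown. The stated 78% and 95% power can be neither confirmed nor refuted from the article. The primary efficacy comparison is untouched. This is a cheap improvement to a named objective.

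**What to change.** Replace the two-stage residual analysis with one-stage regressions:

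- Regress the 3-month mediator on group, baseline mediator, baseline outcome and time since injury, plus the section 20a covariates.
- Regress the 3-month outcome on the same terms plus the 3-month mediator.
- Include these terms whether or not the arms are balanced on them, and say explicitly that the 20a covariates apply to the mediation models.
- Keep the bootstrap interval for ab.
- Add time since injury to the latent growth model.
- State the assumption of no unmeasured mediator-outcome confounding, and add a sensitivity analysis for it.

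**Cost.** All the variables are already planned as baseline data. The change uses a few degrees of freedom out of 200. The stated mediation power was computed on residualised scores, so it becomes approximate and should be described that way or recalculated. The sensitivity analysis is a small amount of extra work.

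### The longitudinal mediation equations omit initial symptoms from the outcome's own rate and asymptote, so symptom persistence can be reported as mediation when treatment moves the mediator

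*Protocol article*

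**What the plan says.** The second set of mediation analyses (Protocol article, Methods for additional analyses {20b}) fits exponential-decay curves to mediator and outcome. Each curve has an initial value, a rate and an asymptote: β0, β1, β2 for the mediator and γ0, γ1, γ2 for the outcome. Step 2 links them with treatment X. In compact form the printed predictors are:

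| Growth factor | Predictors printed |
|---|---|
| β0 | X |
| β1 | γ0 (η2), X |
| β2 | γ0 (η3), X |
| γ0 | X |
| γ1 | β0 (η4), β1 (η5), β2 (η6), X |
| γ2 | β0 (η7), β1 (η8), β2 (η9), X |

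The sentence after the equations describes the same structure. It opens "These equations posit that [1] the initial state of outcome process" and names the mediator's rate and asymptote as what γ0 affects. It then says "initial state, rate of change, and asymptote of moderator process affect both rate of change and asymptote of the outcome process". Equations and prose agree, so γ0 was not lost in typesetting. No covariances among the ξ and ε terms are given, either as free or as fixed at zero.

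The first mediation analysis in the same section replaces the 3-month outcome with its residual after prediction from its own baseline.

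**The concern.** By the plan's own equations γ0 shapes the mediator's course. If γ0 also predicts where symptoms settle, or how fast they fall, it is a common cause of the two ends of every mediator-to-outcome path (η5, η6, η8, η9) and is left out of the outcome side. Randomising X does not protect those paths, because the mediator's course is not randomised.

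Mediation by MVPA and by fear avoidance is a stated hypothesis (Objectives {7}), and the Discussion says the answer should guide how treatment is strengthened. A model that credits a mediator with ordinary symptom persistence could point that work the wrong way. The two sets of mediation analyses could also disagree merely because one adjusts the outcome for its baseline and the other does not.

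**Working it through.** The plan states no figure for this model. Its 78% and 95% mediation power figures (Sample size {14}) belong to the single-mediator regression. The check therefore asks what the printed equations return when the mediator truly has no effect on the outcome.

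**Inputs.** From the article: N = 200, 1:1 allocation. Assumed: two-sided 5% tests; standardised growth factors known without error; correlation r of γ0 with each of β1 and β2, 0.2 to 0.5; correlation ρ of γ0 with γ2 (persistence), 0.3 or 0.5; treatment shift in the mediator asymptote a2 = 0.4 SD; ε0 uncorrelated with ε2; β1 and β2 related only through γ0.

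**Step 1: false coefficient.** Within arm, corr(β1, β2) = r² and corr(β1, γ2) = corr(β2, γ2) = ρr. Regressing γ2 on both without γ0 gives equal coefficients b with b + r²b = ρr, so the false η9 = ρr/(1 + r²).

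| r | ρ = 0.5 | ρ = 0.3 |
|---|---|---|
| 0.2 | 0.10/1.04 = 0.10 | 0.06/1.04 = 0.06 |
| 0.3 | 0.15/1.09 = 0.14 | 0.09/1.09 = 0.08 |
| 0.4 | 0.20/1.16 = 0.17 | 0.12/1.16 = 0.10 |
| 0.5 | 0.25/1.25 = 0.20 | 0.15/1.25 = 0.12 |

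The true value is 0 throughout.

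**Step 2: false indirect effect.** a2 × η9 at ρ = 0.5 runs from 0.4 × 0.096 = 0.04 SD to 0.4 × 0.20 = 0.08 SD. The true total effect is zero, so an equal direct effect of opposite sign offsets it.

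**Step 3: how often it is significant.** For r = ρ = 0.5:

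- Residual variance of γ2 is 1 − 2(0.25)²/1.25 = 0.90, and the variance inflation is 1/(1 − 0.5⁴) = 1.067.
- SE(η9) = √(0.90 × 1.067/200) = 0.069, so z = 0.20/0.069 = 2.9 and the rejection rate is about 82%.
- For the treatment leg, SE = 2√(0.75/200) = 0.122, so z = 0.4/0.122 = 3.3 and power is about 90%.
- Both legs: 0.82 × 0.90 ≈ 74%.

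Simulation with 4,000 trials per setting at ρ = 0.5 agrees:

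| r | η9 significant, γ0 omitted | Both legs, γ0 omitted | η9 significant, γ0 included |
|---|---|---|---|
| 0.2 | 27% | 22% | 5% |
| 0.3 | 49% | 41% | 5% |
| 0.4 | 68% | 59% | 4% |
| 0.5 | 81% | 74% | 5% |

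With γ0 included, both legs are significant in about 4%. At ρ = 0.3 with γ0 omitted, η9 is significant in 12% (r = 0.2) and 31% (r = 0.4). The lowest corner for both legs is about 0.12 × 0.83 ≈ 10%, where 0.83 = 0.224/0.271 is the treatment-leg power at r = 0.2. Runs scatter by a point or two, hence roughly 9–75% overall.

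**Step 4: does measurement error rescue it?** No. The latent model was fitted by maximum likelihood to a population covariance with 9 outcome and 4 mediator visits. This version kept only the asymptote path and held decay rates fixed, with a2 = 0.5.

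| r, ρ | False mediator-to-asymptote coefficient | False indirect effect (SD) |
|---|---|---|
| 0.3, 0.5 | 0.175 | 0.088 |
| 0.5, 0.5 | 0.290 | 0.145 |
| 0.5, 0.7 | 0.411 | 0.205 |

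The matching error-free coefficients (r × ρ) are 0.15, 0.25 and 0.35, so the latent fit gives slightly more bias. Adding the γ0 → γ2 path, or freeing cov(ε0, ε2), returns 0.000 in every case.

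**The case against.** Several points on the other side stand.

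- **Disturbance covariances.** The bias needs ε0 to be uncorrelated with ε1 and ε2, which the article does not say. Its general HBI trajectory model (Statistical methods {20a}) gives the subject-level parameters an unrestricted Σ. Freeing these covariances removes the bias. But Step 2 prints a full set of directed paths and no covariances, and nothing carries Σ into it, so an analyst coding it as printed would get the bias.
- **Not all persistence.** A reader might infer that baseline symptoms can reach later symptoms only through the mediator. They cannot be said to: the outcome curve carries γ0 directly into early values, fading as exp(−γ1t). Only persistence in rate and asymptote is at issue.
- **A false path is not yet false mediation.** If X does not move the mediator, the false indirect effect is zero (5% by joint test, 2% by Sobel). If γ0 does not affect the mediator, there is no bias.
- **The ICC.** The power section's "an ICC = 0.5 for moderate within-subject correlations" describes repeated raw scores, not a γ0–γ2 correlation. It makes some persistence plausible but does not supply ρ.
- **The missing η1.** A reader might take the numbering from η2 as proof of a dropped term. The numbering in the outcome equations (η4 to η9) is unbroken, so it proves nothing.
- **The test used.** Joint significance is more liberal than Sobel, which the article names for the single-mediator model. With a one-path version and a2, r, ρ of (0.3, 0.3, 0.5) and (0.5, 0.3, 0.5), the false rates are 35% and 55% by joint test and 15% and 37% by Sobel.
- **Covariates.** The article promises adjustment for symptom severity in later regressions, but Step 2 prints no covariates. Adjusting only for a binary severity stratum still leaves η9 falsely significant in about 9–30% at ρ = 0.5.

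**Conclusion.** The point holds in limited form. As printed, the model omits a common cause on the mediator-to-outcome paths. If initial symptoms also predict the later symptom rate or plateau, and treatment moves the mediator, part of that persistence is reported as mediation. Under the assumed values, both legs are falsely significant in roughly 9–75% of trials, against about 4–5% with γ0 included. The range depends on r, ρ and the treatment shift, none of which the article gives, and on error-free factors and uncorrelated ε terms.

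A reader might infer that the trial's main result is at risk, or that false mediation is certain. Neither follows. This is the second of two additional mediation analyses, the single-mediator analysis does adjust the outcome for its baseline, and the primary comparison is untouched. The correction should be made before the mediation model is fitted, but it is not a defect that invalidates the trial.

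**What to change.** Add γ0 as a predictor in the γ1 and γ2 equations. Equivalently, state that ε0 covaries freely with ε1 and ε2. Amend the explanatory sentence to match and change *moderator* to *mediator* there. Define the indirect effects from the corrected model, and carry the same rule into whatever growth form is finally chosen for each mediator.

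The cost is a few extra parameters and slightly wider intervals, with no new data. Adding β0 to the β1 and β2 equations, or letting same-visit residuals of mediator and outcome covary, is optional and not needed to cure this problem.
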